#### Treatment preference

During the research interview and prior to treatment allocation, participants will be informed about the two available treatment conditions and will be asked to indicate their preferred condition. Participants will also provide a primary reason for their decision before being informed of their treatment allocation. Participants who choose a condition incongruent with their allocation will be asked if the outcome affects their decision to join the trial. This information will be used to inform potential bias from participants being allocated to their preferred condition.

#### Randomisation acceptability

Once participants state their treatment preference and are informed of their actual treatment allocation, they will be asked whether being randomised to that condition increases the probability of them withdrawing from the study. This information, combined with the recruitment metrics, will be used to estimate the recruitment period and inform whether randomisation in a definitive trial would negatively impact on uptake.

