### The current study

The primary aim of the current study, offering face-to-face counselling, is to demonstrate whether discussion and guided use of a well-being app can be integrated into counselling sessions with university students experiencing anxiety or depression. This feasibility metric will be assessed through evaluation of therapeutic discussion from counselling audio recordings, telephone interviews with participants and a focus group with counsellors. Through this primary aim, the current study will also evaluate feasibility factors related to recruitment, acceptability, intervention delivery and clinical outcome monitoring. Therefore, the primary feasibility outcomes will comprise (i) recruitment duration to reach target sample size, (ii) client treatment preferences, (iii) acceptability of randomisation, (iv) intervention fidelity, (v) client/counsellor satisfaction and (vi) completion rate of follow-up measures. Secondary aims will explore the preliminary impact (in terms of effectiveness) and potential moderators for a fully powered definitive RCT. Preliminary impact will be assessed by comparing differences in therapeutic alliance between TAU and the enhanced intervention condition, as well as capturing participants’ views on the impact counselling has had on their well-being and ability to cope at university. Potential intervention moderators will include app usage during and between counselling sessions, as well as client characteristics.

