## Methods/Design

### Study design

The feasibility trial utilises a two-arm, parallel non-randomised design comparing counselling alone (TAU) versus counselling supplemented with guided use of a well-being app and discussion of app activities (enhanced intervention) for university students experiencing anxiety or depression. This is displayed in Fig. 1. The feasibility trial was registered on the BioMed Central ISRCTN registry on 20/06/2016 under the acronym CASELOAD (Counselling plus Apps for Students Experiencing Levels Of Anxiety or Depression).

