### Recruitment

In line with routine practice, students who approach the counselling service will be assessed by a counsellor to determine their appropriateness for counselling. Students who are approved for counselling (based on clinical judgement) will be provided with a study information booklet and invited to attend a 20-min research interview onsite to determine their eligibility. Leaflets, booklets and posters will also be displayed in the waiting room to raise awareness of the trial and encourage students to volunteer. Students who attend the research interview will be asked to provide written informed consent and will be assessed for eligibility through completion of the PHQ-9 and GAD-7. Eligible participants will be allocated to either the TAU condition or enhanced intervention according to the clinical judgement of the counsellor that provided the initial assessment.

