### Allocation

This study is a non-randomised feasibility trial that aims to address the acceptability of randomisation prior to planning a pilot trial in preparation for a future definitive trial. Therefore, allocation will be based on counsellors’ clinical judgement of each student’s unique situation and primary reason for approaching the service. This will inform the acceptability and feasibility of randomising for the pilot trial. Participant allocation will also depend on whether the assessing counsellor is involved in the trial (based on availability) and whether the counsellor is participating in the provision of the enhanced intervention or TAU condition. Because the enhanced intervention relies on counsellors that are committed and trained to supplement counselling with a well-being app, participants assessed by counsellors in the TAU condition will not have the opportunity to join the enhanced intervention. However, participants assessed by counsellors in the enhanced intervention may be allocated to either condition as determined by their counsellor. Similarly, participants assessed by counsellors providing the enhanced intervention for whom the app is deemed inappropriate (e.g. client presents with inappropriate/excessive technology use or risk negative exposure to online communities for self-harm) will be allocated to TAU.

Considering these design elements, allocation will depend on the following factors: (i) whether the initial clinical assessment is with a counsellor who is part of the trial; (ii) whether the assessing counsellor is allocated to provide the enhanced intervention or TAU condition; (iii) the clinical judgement of the counsellor regarding whether participating in the trial would be appropriate for the client; and (iv) the clinical judgement of the counsellor regarding which intervention would be appropriate for the client. Whilst this allocation procedure is reliant on a counsellor’s clinical judgement, it is arguably the most appropriate allocation method for a non-randomised study and it keeps the client’s welfare in the forefront. Integrating a well-being app with face-to-face counselling with students experiencing moderate anxiety or depression is a new development with limited understanding of the implications. Therefore, using clinical judgement to inform the allocation will better monitor risk and feasibility metrics which counsellors will document to inform the screening criteria of a future randomised trial.

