### Primary feasibility measures

The yield of the feasibility trial is a series of specific primary and secondary outputs relating to a range of components that will inform the definitive trial. The primary outputs are recruitment, treatment preference, randomisation acceptability, treatment satisfaction and completion rate of follow-up measures. The secondary outputs are: app usage, intervention fidelity, client characteristics, therapeutic alliance and academic coping. Each of these primary and secondary outputs is described next.

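### Randomisation acceptability, a primary outcome, is measured by a post-disclosure question about a randomisation that did not take place, so it informs only indirectly on willingness to accept chance allocation

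*Protocol article*

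**What the plan says.** The aims (The current study) list "iii) acceptability of randomisation" among the primary feasibility outcomes, and Primary feasibility measures repeats that status: "The primary outputs are recruitment, treatment preference, randomisation acceptability, treatment satisfaction and completion rate of follow-up measures".

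Study design describes a "two-arm, parallel non-randomised design". Recruitment says that eligible students go to an arm "according to the clinical judgement of the counsellor that provided the initial assessment", and Allocation says that "allocation will be based on counsellors’ clinical judgement of each student’s unique situation and primary reason for approaching the service". Allocation adds a structural rule: a client assessed by a counsellor who delivers TAU cannot enter the enhanced arm, whereas a client assessed by an enhanced-arm counsellor may go to either arm.

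The outcome is defined operationally only under Randomisation acceptability. After clients have stated a preference and learned their actual allocation, "they will be asked whether being randomised to that condition increases the probability of them withdrawing from the study". The answer, read together with recruitment data, is to help estimate the recruitment period and to show whether randomising in a definitive trial would harm uptake.

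Under Treatment preference, clients state a preferred arm in the research interview, and "Participants will also provide a primary reason for their decision before being informed of their treatment allocation". Clients whose allocation differs from their preference are then asked whether this changes their decision to join.

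**The concern.** To accept randomisation is to agree, before the arm is known, that chance will settle it. The planned item asks something else: whether one arm, already disclosed and not assigned by chance, makes leaving more likely. A client can be content with the arm received and still unwilling to be randomised. A client can also be disappointed with that arm and yet have been willing to let chance decide.

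Addressing the acceptability of randomisation is a stated purpose of this non-randomised design, and the result is meant to feed the planning of the next trials. As defined, the study could report a primary result under that name without having put the question directly to anyone. No later analysis can recover an answer that was not collected before disclosure.

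**Working it through.** The article states no target proportion, power or precision for this outcome, so there is no figure to reproduce. The check sets the sections side by side.

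1. **Premise.** Study design, Recruitment and Allocation describe no random element. The number of participants randomised is 0 of 40, so the phrase about being randomised to a condition is untrue for 40 of 40.

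2. **Timing.** The item under Randomisation acceptability follows disclosure of the arm. The preference and its reason are taken before disclosure, so the same interview already contains a suitable moment for a question about chance allocation. No such question is described there.

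3. **Overlap.** With the arm known, the item differs little from the one under Treatment preference for clients with a mismatched allocation. One asks about joining and the other about withdrawing, and both record a reaction to the arm received.

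4. **Event.** The item asks about withdrawal from this study. The stated inference concerns uptake of a future randomised one.

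5. **Respondents.** "Students who attend the research interview will be asked to provide written informed consent", and the study they are invited to is not randomised. Students who do not come to the interview are not asked. Any answer describes attendees, not all students invited.

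6. **Direction of bias.** Let m be the share of clients whose allocation differs from their preference. Let a_c and a_i be the shares reporting no added wish to withdraw among matched and mismatched clients. The item then returns

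   A = (1 − m) × a_c + m × a_i.

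   Suppose that mismatch makes withdrawal more attractive, so that a_i < a_c (an assumption). A then falls as m rises. Counsellors who fit the arm to the client may lower m. The rule that clients of TAU counsellors cannot have the app may raise m, if many of them want it. The article gives none of m, a_c or a_i. It also gives nothing that links A to W, the share who would accept chance allocation before knowing the arm. The sign of A − W therefore cannot be determined, and neither can its size.

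**The case against.** The strongest defence is that the article reports the question in indirect speech and does not show the wording put to clients. Allocation openly says that a non-randomised study will examine the acceptability of randomisation, so a hypothetical reading (suppose you had been randomised to this arm) is plausible. That stands in part, and it is why the item has some indirect value: it shows how clients react to an arm they did not prefer. Even so read, it remains conditional on a known arm.

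Three stronger readings are tempting, and the documents do not support them.

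- *A reader might infer that acceptability will be overstated.* Fitting the arm to the client and asking only attendees point that way. Being told a non-preferred arm can equally depress the answer. With no mismatch rate stated, the direction is open, and any percentage put on the error would be invented.
- *A reader might infer that the counsellors' side goes unexamined.* Allocation has counsellors document risk and feasibility information for the screening criteria of a future randomised trial, and Qualitative analysis adds clinical notes and a focus group. This does not measure clients' acceptance, but it is not nothing.
- *A reader might infer that a wrong uptake figure would pass straight into the definitive trial.* The answer is one input among several, is analysed descriptively and has no stated progression threshold. A randomised pilot is planned first and would observe uptake under actual randomisation.

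It can also be said that a journal article condenses. That does not answer the point, which is not an omission: the item, its timing and its use are all stated, and they do not fit together.

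**Conclusion.** The concern holds in a limited form. The stated item rests on a premise that is untrue for every participant. It is asked once the arm is known, and it measures a reaction to the allocation received. It gives only indirect evidence on willingness to accept chance allocation and on the effect of randomisation on uptake.

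The mismatch in construct affects the whole of this one primary outcome. Its numerical effect cannot be estimated from the document, and its direction is unknown. The conclusion rests on the article's description being a fair account of the question as asked. It needs no assumption about response rates. This is a correction to one instrument, not a flaw in the choice of a non-randomised design, and it is worth making because the outcome is primary and the question can be put only before disclosure.

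**What to change.** 1. In the research interview, next to the preference question and before allocation is disclosed, ask every attendee whether they would take part if their treatment were decided by chance, and record the reasons.
2. Report randomisation acceptability from that item, and state that it applies to interview attendees only.
3. Keep the existing post-disclosure question, but remove the reference to having been randomised and relabel it *acceptability of the allocation received*. Report it alongside the question on mismatch with preference.
4. Optionally, have the assessing counsellor tick for each client whether random allocation would have been acceptable, with a reason.

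The cost is one or two interview items and a minor amendment. Treatment, allocation and sample size stay as they are.

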#### Treatment satisfaction

Participant treatment satisfaction will be assessed with the 8-item Client Satisfaction Questionnaire (CSQ-8) [27], which will be emailed to participants the day after their last counselling session. CSQ-8 items refer to a client’s overall service experience and are rated on a 4-point Likert scale (1 = “quite dissatisfied”; 5 = “very satisfied”) whereby higher scores indicate greater satisfaction. Many counselling services report on client satisfaction to allow comparison to other services and to ensure that services respond to client feedback. Capturing client satisfaction will also allow comparisons between treatment conditions to explore whether the enhanced intervention had a positive or negative impact on a participant’s service experience. A sub-sample of participants’ service experiences will also be explored through telephone interviews after counselling completion. Finally, counsellor satisfaction in the delivery of the enhanced intervention will be assessed through a focus group once all participants have completed counselling.

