### Measures

The timeframe for administering measures has been summarised in Table 1 and in a Standard Protocol Items: Recommendations for Interventional Trials (SPIRIT) diagram in Fig. 2. The clinical outcome measures and primary and secondary feasibility measures have been detailed below.

**Table 1 Tab1:** Summary and timeframe of measure administration

Measure	Clinical assessment	Consent session	S1	S2	S3	S4	S5	S6	Last session^a^	3-month follow-up	6-month follow-up
CORE-10	×		×	×	×	×	×	×	×		
CCAPS-62	×										
CCAPS-34			×	×	×	×	×	×	×		
PHQ-9		×								×	×
GAD-7		×								×	×
CD-RISC 10		×								×	×
WAI-12					×						
CSQ-8									×		

^a^This may be any session number beyond session 2 as the number of sessions will vary across clients and will be dependent on client-counsellor agreement

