### Statistical analyses

#### Quantitative analysis

Analyses will be predominantly descriptive to characterise the study population and outline various feasibility metrics including recruitment rate, treatment preference, randomisation acceptability, treatment satisfaction and completion at follow-up. Whilst the sample size is not powered to detect significant differences between the TAU and enhanced intervention groups, data will be used to summarise outcomes from both groups to reveal preliminary trends and inform the design of the pilot trial from which estimates of effect and sample sizes will be calculated. Group comparisons will also be made between the demographic and baseline clinical measures to characterise the groups when they enter the trial. Determining potential baseline differences between the groups will inform whether the allocation procedure, which was dependent on clinical judgement, unintentionally created differences between the groups. Establishing these differences, or lack thereof, will further inform the potential group differences in clinical outcomes at the end of the feasibility trial. Outcome data will include the baseline prevalence and subsequent changes in depression (PHQ-9), anxiety (GAD-7), psychological functioning (CORE-10), student-specific mental health concerns (CCAPS) and emotional resilience (CD-RISC 10). Group summaries will also compare levels of therapeutic alliance (WAI) and treatment satisfaction (CSQ-8) in order to inform preliminary differences across treatments. No interim analysis will be performed; analysis will commence after completion of the 6-month follow-up. The distribution, variance and skewness of data will be initially explored to determine whether data should be described with parametric or non-parametric methods. Parametric descriptive statistics will include total score, mean, standard deviation, min, max and range. Non-parametric descriptive statistics will include total score, median, confidence intervals and inter-quartile ranges. Quantitative analyses will be performed with SPSS statistical software (version 22.0).

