Approximately 40 h of therapy is anticipated to be recorded, transcribed and analysed. The conservative estimation for recordings considers several factors including the following: (1) although participants will be offered ~6 counselling sessions, the services’ median number of attended sessions is 2 and 4; (2) participants (and therapists) may decide not to record a session where the participant is particularly distressed; (3) trial budget available to fund transcription; and (4) feasibility trials are not required to be powered to detect significant effects but to provide sufficient preliminary indicators. Whilst data from the therapy recordings is qualitative in nature, they will be analysed with “quantitative” content analysis [29] whereby sessions will be scored to indicate intervention fidelity and implementation success. These scores will be achieved by using a checklist developed from the training materials to rate the extent to which therapists delivered the new intervention (see “Intervention fidelity” section). A random sample of 15 therapy hours will be assessed by an independent researcher, blind to the aims of the study, to permit analysis of inter-rater reliability.

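### CSQ-8, a primary feasibility output, is described as a 4-point scale anchored 1 to 5, and it is unclear whether participants ending at session 1 or 2 receive it

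*Protocol article*

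**What the plan says.** In the Protocol article, Primary feasibility measures: "The primary outputs are recruitment, treatment preference, randomisation acceptability, treatment satisfaction and completion rate of follow-up measures". The Treatment satisfaction section names the instrument: "Participant treatment satisfaction will be assessed with the 8-item Client Satisfaction Questionnaire (CSQ-8"). Its items are "rated on a 4-point Likert scale (1 = “quite dissatisfied”; 5 = “very satisfied"), with higher scores meaning greater satisfaction. The same section gives comparison with other services as a reason for reporting satisfaction and says that the two conditions will be compared. The Quantitative analysis section repeats the comparison: "Group summaries will also compare levels of therapeutic alliance (WAI) and treatment satisfaction (CSQ-8").

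On timing, the Treatment satisfaction section describes a form "which will be emailed to participants the day after their last counselling session", with no minimum number of sessions. Table 1 (Measures) marks CSQ-8 in one column only, the last session, and footnote a says of that column: "This may be any session number beyond session 2 as the number of sessions will vary across clients". The Quantitative analysis section, when estimating hours of recordings, notes that "the services’ median number of attended sessions is 2 and 4".

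**The concern.** There are two separate problems with the same outcome.

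First, the response format contradicts itself. The number of options and the top anchor fix the range of the total score. A reader of the results cannot place a mean CSQ-8 total, or set it beside another service's figure, without knowing that range.

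Second, Table 1 and the text give different answers for a participant whose last session is session 1 or 2. The text would send the form. The footnote, read literally, leaves that person with no last session and hence no CSQ-8. If the footnote were applied that way, satisfaction would be summarised and compared between arms only among those who stayed. The Discussion says that the study hopes to show a preliminary impact on drop-out, so staying may itself depend on the arm, and the two groups compared could be selected differently.

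**Working it through.** **Response format.** Inputs from the Treatment satisfaction section: 8 items, stated as 4-point, anchors 1 and 5.

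- Points per item = high − low + 1 = 5 − 1 + 1 = 5. The stated 4 is not reproduced.
- Total with four options (1 to 4): 8 × 1 = 8 to 8 × 4 = 32, midpoint 20.
- Total with five options (1 to 5): 8 × 1 = 8 to 8 × 5 = 40, midpoint 24.

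Position of the same raw total on each range, as (total − 8) / (maximum − 8):

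| Total | On 8–32 | On 8–40 |
|---|---|---|
| 24 | 16/24 = 67% | 16/32 = 50% |
| 28 | 20/24 = 83% | 20/32 = 63% |
| 32 | 24/24 = 100% | 24/32 = 75% |

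The other rating scales in the article pass the same count: CORE-10, CCAPS and CD-RISC 10 run 0 to 4 and are called 5-point; PHQ-9 and GAD-7 run 0 to 3 and are called 4-point; the WAI runs 1 to 5 and is called 5-point. Only CSQ-8 fails.

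**Who receives the form.** For each possible last session:

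| Last session attended | Treatment satisfaction section | Table 1 with footnote a, read literally |
|---|---|---|
| 1 or 2 | sent the next day | no last session, so no CSQ-8 |
| 3 to 6 | sent the next day | sent |

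The two sources differ only in the first row, and no other section decides between them.

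**How many could be affected.** The documents give no trial figure. The service median is stated as two values, with no explanation of what each refers to. If a median of 2 applied to the trial, at least half of the 40 participants (20 or more) would attend two sessions or fewer. If a median of 4 applied, at least half would attend four or more, so at most 20 would end by session 2. For assumed shares of 10%, 25% and 50% ending by session 2, the counts are 0.10 × 40 = 4, 0.25 × 40 = 10 and 0.50 × 40 = 20.

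**What a literal reading would do.** In one arm, let p be the share ending by session 2 and d the mean CSQ-8 of stayers minus that of early leavers. The full mean is the stayers' mean − p × d, so reporting stayers alone shifts the arm's mean by p × d. The shift in the difference between arms is p₁d₁ − p₂d₂, where 1 and 2 denote the arms. It is zero if p and d are equal in both. The documents give neither p nor d, so neither sign nor size can be stated.

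**The case against.** **On the scale.** CSQ-8 is a named, cited instrument. The online form would probably be built from the instrument and not from this sentence, and both arms would presumably receive the same form, so the comparison between arms would be on one scale whichever is meant. That stands as a limit on the consequence: the percentages above show what a misread range could do, not an expected error. It does not remove the contradiction in how a primary output is scored, and comparison with other services still needs a known range.

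**On the footnote.** A reader might infer that Table 1 excludes early leavers from the satisfaction measure. The documents do not support that. The footnote explains why the last session falls at different numbers for different clients; it does not say who is sent the form, and the operative text sets no minimum. What stands is a conflict to reconcile.

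**On the other measures in that column.** A reader might also infer that the final CORE-10 and CCAPS-34 are lost for early leavers. They are not: Table 1 marks both at every session from session 1 to session 6, so someone leaving after session 1 or 2 already has a score from the last session attended. Only CSQ-8 depends on that column alone.

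**On unplanned endings.** For a drop-out, the last session is recognised as such only afterwards. How that is handled is operational detail that an article may leave to the full protocol, so its absence is not held against the plan. It is, however, a reason why a later re-send is useful.

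**Conclusion.** The response-format contradiction is certain: four options and anchors of 1 and 5 cannot both hold, and the total is 8–32 or 8–40 accordingly. The article does not show which is intended.

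The second point holds as an ambiguity: the documents conflict on whether participants ending at session 1 or 2 receive CSQ-8. That group could be large given the service median, but its size in the trial is unknown. It would be wrong to say that up to half the sample is lost. The median is an unclear, service-level figure used to estimate recording hours, and a median of 2 would imply at least half, not at most half. It would also be wrong to say that satisfaction is inflated: that requires early leavers to be less satisfied and the footnote to be applied as a rule, and the documents establish neither.

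The impact is bounded because the analysis is mainly descriptive and "the sample size is not powered to detect significant differences between the TAU and enhanced intervention groups". Describing the feasibility outputs correctly is nonetheless the purpose of this trial, so both points should be corrected.

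**What to change.** 1. In the Treatment satisfaction section, state the number of response options, both anchors and the total-score range so that they agree with each other and with the form actually used.
2. Reword footnote a of Table 1 so that the last session is the last session attended, counting from session 1, in line with the text.
3. Re-send CSQ-8 with the 3-month online survey to anyone who has not yet returned it.
4. Report the CSQ-8 response by arm and by number of sessions attended. The Completion rate of follow-up measures section counts the 3-month measures, the 6-month measures and the telephone interviews, so without this step loss of CSQ-8 would not show in the planned completion figures.

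Items 1 and 2 are wording changes. Item 3 adds eight questions, for some participants, to a survey that is already emailed. Item 4 is one extra table. The downside is that those who answer at the re-send do so somewhat later after their last session than the others, so the time of response should be recorded.
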